### 15.2.1.3 Adolescent Baseline

We want to ask some basic questions about you:

1. Your current age in years:
2. The sex assigned to you at birth
  - a. Female
  - b. Male
  - c. Intersex
  - d. Prefer not to answer
3. Your race (please select one):

- a. American Indian or Alaskan Native
  - b. Asian
  - c. Black or African American
  - d. Hispanic or Latino
  - e. Middle Eastern or North African
  - f. Native Hawaiian or Other Pacific Islander
  - g. White
  - h. Prefer not to answer
4. The language you mainly use your home:
- a. English
  - b. Spanish
  - c. Other: \_\_\_\_\_
5. Your current grade (year) in school:
- a. 5th
  - b. 6th
  - c. 7th
  - d. 8th
  - e. 9th
  - f. 10th
  - g. 11th
  - h. 12th
  - i. Other: \_\_\_\_\_

#### 15.2.1.4 Adolescent Alterations in Taste and Other Treatment-Related Symptoms

Thank you for agreeing to be in this research study. Our goal is to find ways to better support children and their families during the child's treatment with chemotherapy.

The first questions ask about taste changes some adolescents have after chemotherapy. Please click the circle that best describes how much that taste change **bothered you this week**.

|                                   | Not at all | A little | Medium | A lot | Extremely |
|-----------------------------------|------------|----------|--------|-------|-----------|
| Difficulty tasting sweet          |            |          |        |       |           |
| Difficulty tasting salty          |            |          |        |       |           |
| Difficulty tasting sour           |            |          |        |       |           |
| Difficulty tasting bitter         |            |          |        |       |           |
| Difficulty tasting flavors        |            |          |        |       |           |
| Everything tastes bad             |            |          |        |       |           |
| Food doesn't taste like it should |            |          |        |       |           |
| Bitter taste in my mouth          |            |          |        |       |           |
| Bad taste in my mouth             |            |          |        |       |           |
| Metal taste in my mouth           |            |          |        |       |           |
| Can't eat hot food                |            |          |        |       |           |

|                      |  |  |  |  |  |
|----------------------|--|--|--|--|--|
| Can't eat spicy food |  |  |  |  |  |
| Can't eat meat       |  |  |  |  |  |

Please tell us about any other taste changes that bothered you this week by writing them here:  
[insert text box]

The next questions are about other treatment-related symptoms adolescents can have. Please tell us how much each of these things **bothered you yesterday or today** by clicking the circle that best describes that amount:

|                                       | Not at all | A little | Medium | A lot | Extremely |
|---------------------------------------|------------|----------|--------|-------|-----------|
| Feeling disappointed or sad           |            |          |        |       |           |
| Feeling scared or worried             |            |          |        |       |           |
| Feeling cranky or angry               |            |          |        |       |           |
| Problems with thinking or remembering |            |          |        |       |           |
| Changes in how your body or face look |            |          |        |       |           |
| Feeling tired                         |            |          |        |       |           |
| Mouth sores                           |            |          |        |       |           |
| Headache                              |            |          |        |       |           |
| Hurt or pain (other than headache)    |            |          |        |       |           |
| Tingly or numb hands or feet          |            |          |        |       |           |
| Throwing up or feeling like you might |            |          |        |       |           |
| Changes in taste                      |            |          |        |       |           |
| Constipation (hard to poop)           |            |          |        |       |           |
| Diarrhea (watery, runny poop)         |            |          |        |       |           |

Please tell us about any other things that bothered you this week by writing them here:

## 15.2.2 PARENTAL SURVEYS

### 15.2.2.1 Food Insecurity

These statements are what people have said about their food situations. Please tell us whether the statement was often true, sometimes true, or never true for you in the last 6 months.

1. "The food that I bought just didn't last, and I didn't have money to get more."
    - a. Often true
    - b. Sometimes true
    - c. Never true
    - d. Don't know or prefer not to answer
  2. "We couldn't afford to eat balanced meals."
    - a. Often true
    - b. Sometimes true
    - c. Never true
-

- d. Don't know or prefer not to answer
- 3. In the last 3 months, did you or other adults in your household ever cut the size of your meals or skip meals because there wasn't enough money for food?
  - a. Yes
  - b. No (Skip AD1a)
  - c. Don't know or prefer not to answer (Skip AD1a)

[If YES above, then]

- 4. How often did this happen – almost every month, some months, but not every month, or in only 1 or 2 months?
  - a. Almost every month
  - b. Some months but not every month
  - c. Only 1 or 2 months
  - d. Don't know or prefer not to answer
- 5. In the last 3 months, did you ever eat less than you felt you should because there wasn't enough money for food?
  - a. Yes
  - b. No
  - c. Don't know or prefer not to answer
- 6. In the last 3 months, were you ever hungry but didn't eat because there wasn't enough money for food?
  - a. Yes
  - b. No
  - c. Don't know or prefer not to answer

#### 15.2.2.2 *Nutrition Insecurity*

The following questions ask about your household's ability to decide what you eat

- 7. In the last 3 months, we had to eat foods that were not good for our health and well-being because we couldn't get other types of food
    - a. Never
    - b. Rarely
    - c. Sometimes
    - d. Often
    - e. Always
    - f. Don't know or prefer not to answer
  - 8. In the last 3 months, we know there were things we should or should not eat for our health and wellbeing, but we could not get healthful food.
    - a. Never
    - b. Rarely
    - c. Sometimes
    - d. Often
-

- e. Always
  - f. Don't know or prefer not to answer
9. In the last 3 months, we worried that the food we were able to eat would hurt our health.
- a. Never
  - b. Rarely
  - c. Sometimes
  - d. Often
  - e. Always
  - f. Don't know or prefer not to answer
10. In the last 3 months, we had to eat the same thing for several days because we didn't have money to buy other food.
- a. Never
  - b. Rarely
  - c. Sometimes
  - d. Often
  - e. Always
  - f. Don't know or prefer not to answer
11. In the last 3 months, we could control if we were able to eat quality food.
- a. Never
  - b. Rarely
  - c. Sometimes
  - d. Often
  - e. Always
  - f. Don't know or prefer not to answer
12. In the last 3 months, we could control if we were able to eat foods good for our health.
- a. Never
  - b. Rarely
  - c. Sometimes
  - d. Often
  - e. Always
  - f. Don't know or prefer not to answer

*15.2.2.3 Parent-Reported Acceptability, Appropriateness, Feasibility, Affordability, & Accessibility*

These questions ask your opinions about the Medically Tailored Meals for Kids (MTM-Kids) program. Please select the response that best fits your thoughts.

---

Please provide the following information for study-related communications

Mobile phone number (XXX) XXX -XXXX

Preferred contact method for study reminders and surveys (check one):

|              |       |
|--------------|-------|
| Mobile phone | Email |
|--------------|-------|

Best days of the week to contact you (check all that apply)

\_\_\_ Monday \_\_\_ Tuesday \_\_\_ Wednesday \_\_\_ Thursday \_\_\_ Friday \_\_\_ Saturday \_\_\_ Sunday

Best time(s) of day to reach you (check all that apply)

\_\_\_ Morning \_\_\_ Afternoon \_\_\_ Evening

Your home address

House number:

Street name:

City:

Zip code:

### 15.2.2.5 Financial Coping Strategies

Due to changes in your household expenses and work, have you done any of the following since your child was diagnosed (please select all that apply)?

|                                                                                  | Never | Sometimes | Often | I don't have this |
|----------------------------------------------------------------------------------|-------|-----------|-------|-------------------|
| Use savings                                                                      |       |           |       |                   |
| Use retirement funds                                                             |       |           |       |                   |
| Take out a loan or increase credit card debt                                     |       |           |       |                   |
| Get another job, or increase work hours                                          |       |           |       |                   |
| Not take a new job or opportunity because of worry about losing health insurance |       |           |       |                   |
| Receive money from fundraisers or crowdfunding                                   |       |           |       |                   |
| Cut back on putting in retirement or education accounts                          |       |           |       |                   |
| Move to reduce mortgage or rent                                                  |       |           |       |                   |
| Cut back on spending for vacation, travel, or relaxation                         |       |           |       |                   |
| Cut back on spending for afterschool or summer activities for your children      |       |           |       |                   |
| Cut back on spending for family celebrations                                     |       |           |       |                   |
| Cut back on spending for groceries                                               |       |           |       |                   |
| Cut back on spending for healthcare                                              |       |           |       |                   |
| Cut back on spending for necessities for your family, such as clothing           |       |           |       |                   |
| Cut back on spending for education                                               |       |           |       |                   |
| Delay or skip filling prescriptions due to cost                                  |       |           |       |                   |
| Skip or reduce medication doses due to cost                                      |       |           |       |                   |
| Miss medical appointments due to cost                                            |       |           |       |                   |

Are other changes in how you manage your finances that you want to tell us about?

---

### 15.2.2.6 Financial Distress

The following questions are intended to get a sense of how financially secure you feel your family is. Please select the responses **most appropriate** for your situation.

41. What do you feel is the level of your financial stress today?

|                     |   |             |   |            |   |                  |
|---------------------|---|-------------|---|------------|---|------------------|
| 1                   | 2 | 3           | 4 | 5          | 6 | 7                |
| 8                   | 9 | 10          |   |            |   |                  |
| Overwhelming stress |   | High stress |   | Low stress |   | No stress at all |

42. On the stair steps below, mark (with an X) how satisfied you are with **your present financial situation**. “1” at the bottom represents complete dissatisfaction. “10” at the top represents complete satisfaction. The **more dissatisfied** you are, the lower the number you should mark. The **more satisfied** you are, the higher the number you should mark.

A staircase diagram with 10 steps. The bottom step is labeled '1' and 'Dissatisfied'. The top step is labeled '10' and 'Satisfied'. The steps are numbered 1 through 10 from bottom to top.

43. How do you **feel** about your **current financial situation**?

|                  |   |                        |   |             |   |                  |   |   |    |
|------------------|---|------------------------|---|-------------|---|------------------|---|---|----|
| 1                | 2 | 3                      | 4 | 5           | 6 | 7                | 8 | 9 | 10 |
| Feel overwhelmed |   | Sometimes feel worried |   | Not worried |   | Feel comfortable |   |   |    |

44. How **often** do you worry about being **able to meet normal monthly living expenses**?

|                    |   |                 |   |              |   |             |   |   |    |
|--------------------|---|-----------------|---|--------------|---|-------------|---|---|----|
| 1                  | 2 | 3               | 4 | 5            | 6 | 7           | 8 | 9 | 10 |
| Worry All the time |   | Worry sometimes |   | Rarely worry |   | Never worry |   |   |    |

45. How **confident** are you that you could find the money to pay for a **financial emergency** that costs about **\$1,000?**

|               |   |                   |   |                 |   |                 |   |   |    |
|---------------|---|-------------------|---|-----------------|---|-----------------|---|---|----|
| 1             | 2 | 3                 | 4 | 5               | 6 | 7               | 8 | 9 | 10 |
| No Confidence |   | Little Confidence |   | Some Confidence |   | High Confidence |   |   |    |

46. How **often** does this happen to you? You want to go out to eat, go to a movie or do something else and **don't go because you can't afford to?**

|              |   |   |           |   |   |        |   |   |       |
|--------------|---|---|-----------|---|---|--------|---|---|-------|
| 1            | 2 | 3 | 4         | 5 | 6 | 7      | 8 | 9 | 10    |
| All the Time |   |   | Sometimes |   |   | Rarely |   |   | Never |

47. How **frequently** do you find yourself just getting by financially and living **paycheck to paycheck?**

|              |   |   |           |   |   |        |   |   |       |
|--------------|---|---|-----------|---|---|--------|---|---|-------|
| 1            | 2 | 3 | 4         | 5 | 6 | 7      | 8 | 9 | 10    |
| All the Time |   |   | Sometimes |   |   | Rarely |   |   | Never |

48 How **stressed** do you feel about your personal finances **in general?**

|              |   |   |           |   |   |        |   |   |       |
|--------------|---|---|-----------|---|---|--------|---|---|-------|
| 1            | 2 | 3 | 4         | 5 | 6 | 7      | 8 | 9 | 10    |
| All the Time |   |   | Sometimes |   |   | Rarely |   |   | Never |

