Financial wellbeing will be measured by the 8-item Personal Financial Well-being Scale (PFWS). [57] The PFWS uses a 10-point response scale. Scores are calculated by summing item responses and dividing by 8. Scores can range from 1 to 10, with 1 indicating poorest financial wellbeing and 10 indicating highest financial wellbeing. The PFWS has undergone rigorous psychometric testing to establish validity of the latent construct, psychometric properties and norms. [57]

Parent-reported acceptability, appropriateness, feasibility, affordability, and accessibility of the MTM-Kids program will be measured using of the MTM-Kids program will be measured using items developed by others for use in studies examining concerned with the implementation of evidence-based interventions in practice [52] and adapted for this feasibility study. Each domain has 4-items. Parents will be asked to read each item and indicate their response using 5-point scales anchored by 1=completely disagree and 5=completely agree. Domain scores will be calculated by summing item responses and dividing the sum by 4. Domain score range is 1-4, with higher scores indicating better MTM program acceptability, appropriateness, feasibility, affordability, or accessibility. [52]

---

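### Item 48 of the parent financial well-being form asks how stressed the parent feels but prints how-often answers, so one of eight equally weighted items can miss a fall in stress intensity

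*Protocol*

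**What the plan says.** Protocol Section 7.2.2 measures parental financial well-being with an eight-item scale, each item answered from 1 to 10. The responses are summed and divided by 8, which gives a score from 1 (poorest) to 10 (best). The section adds that "The PFWS has undergone rigorous psychometric testing to establish validity of the latent construct, psychometric properties and norms". No item is excluded or scored differently.

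The form is printed in Section 15.2.2.6 as items 41 to 48. Three of them matter most for comparison with the last:

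- Item 41: "41. What do you feel is the level of your financial stress today". Its labels describe intensity: "Overwhelming stress | | High stress | | Low stress | | No stress at all".
- Item 46: "46. How often does this happen to you". Its labels describe frequency: "All the Time | | | Sometimes | | | Rarely | | | Never".
- Item 47: "47. How frequently do you find yourself just getting by financially and living paycheck to paycheck". It has the same frequency labels as item 46.
- Item 48: "48 How stressed do you feel about your personal finances in general". It also has the frequency labels of items 46 and 47.

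Financial well-being is an exploratory outcome, judged by T4 against T1 (Section 3.3.1) and reported with means, ranges, standard deviations and figures (Section 8.3.3).

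**The concern.** The stem of item 48 asks how much; the labels answer how often. A parent under constant but mild money stress has two honest answers: a high number if the stem governs, or 1 if the labels govern. The form does not say which to follow.

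Using the same form at both visits does not remove the problem. A parent who feels stressed all the time at T1 and at T4, but less severely at T4, can mark 1 both times, and the improvement leaves no trace on this item. Parents enter the study by screening positive for household material hardship (Section 5.1), so persistent money stress is plausible in this sample. A parent could also follow the stem at one visit and the labels at the other, which adds noise to an already small data set.

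What is at stake is the accuracy of one component of a scored T1-to-T4 outcome, and the ambiguity cannot be resolved after the answers are in.

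**Working it through.** **Stem against labels.** In items 46 and 47, stem and labels both concern frequency and agree. In item 41, stem and labels both concern intensity and agree. In item 48, the stem concerns intensity and the labels concern frequency. It is the odd one out of these four. The label row under item 48 is complete and well formed as printed, with ten numbers and four labels, so nothing suggests that it is a broken table.

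**Inputs.** Eight items, each 1 to 10, and score = sum / 8 (Section 7.2.2). The protocol gives no expected change or standard deviation for this score, so the changes *d* used below are assumptions.

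**Reproducing the stated range.** Minimum = (8 × 1)/8 = 1. Maximum = (8 × 10)/8 = 10. This matches the stated 1 to 10.

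**Weight of item 48.** 1/8 = 0.125, or 12.5% of the score.

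**Loss if a change of *d* item points fails to register.** Loss on the score = *d*/8.

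| Unregistered change *d* on item 48 | Loss on the 1-10 score |
|---|---|
| 1 | 0.125 |
| 2 | 0.25 |
| 3 | 0.375 |
| 9 (arithmetical ceiling) | 1.125 |

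The ceiling is 1.125/9 = 12.5% of the 9-point range.

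**Relative loss, two patterns.**

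- All eight items would improve by *d*, and item 48 stays flat: the score moves 7*d*/8 instead of *d*, a loss of 12.5%. For *d* = 2, it moves 1.75 instead of 2.
- Only the two stress items (41 and 48) would improve by *d*, and item 48 stays flat: the score moves *d*/8 instead of 2*d*/8, a loss of half. For *d* = 2, it moves 0.25 instead of 0.50.

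**Direction.** The loss arises when intensity falls and frequency does not. If stress became rarer but no milder when present, a parent answering by the labels would register a change in something the stem does not ask about. The mismatch therefore has no fixed sign.

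**The case against.** The strongest reply is that this hardly matters. Frequency and intensity of stress are related, 10 still means best, and the printed form is the same at T1 and T4. Item 41 already records intensity. Items 44, 46 and 47 are frequency items, so the scale mixes both kinds by design. The outcome is exploratory and descriptive, the feasibility benchmarks in Section 8.3.1 do not use it, and the outcomes listed in the opening of Section 8 for sizing the future trial do not name financial well-being.

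Most of this stands, and it limits the importance of the point. It does not remove the mismatch. Item 41 asks about today and item 48 about stress in general, so one does not stand in for the other. A mix of item types is unobjectionable when each item's answers fit its own question.

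Three stronger readings are tempting, and the documents do not support them:

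- **That the item was altered from its source, so that the cited validity and norms no longer apply.** The protocol does not reproduce the published instrument, so it cannot show whether item 48 departs from it. Section 8.3.3 plans no comparison with norms.
- **That the T1-to-T4 change is understated.** It can be, but only if intensity falls while frequency holds.
- **That the loss is as large as 0.75 points.** That figure is (7 − 1)/8. It needs a parent whose stress falls from overwhelming to low yet is constant at both visits, who answers purely by the labels, and intensity labels that sit at 1, 4, 7 and 10. The label positions for item 41 cannot be read reliably from the form as extracted.

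**Conclusion.** The point holds as an error in the form: item 48's stem and answer labels disagree, and the item carries one eighth of the score. Each item point of change that fails to register costs 0.125 on the 1-10 score. The loss is 12.5% of the change if all items would improve equally and item 48 stays flat. It would be half if only the two stress items would move. These figures rest on the scoring rule in Section 7.2.2 and on the assumption that some parents answer by the labels; how many would do so is unknown.

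The item is not worthless, since frequency of stress is related to its intensity. The importance is small: an exploratory outcome, described rather than tested, in about 15 parents, with no feasibility decision attached. It is worth correcting because the correction is easy before data are collected and impossible afterwards.

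**What to change.** Check item 48 against the source instrument, then make its stem and labels agree on the form used at both T1 and T4. If the item is to ask about level of stress, the intensity labels of item 41 are the form's own model. The check should come first, so that the correction does not itself depart from the published scale.

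If any parent has already answered the form as printed, keep that form for the same parent at T4, so that T1 and T4 are answered on one version. Also report the mean of the other seven items (sum / 7, which still runs from 7/7 = 1 to 70/7 = 10).

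The cost is a comparison with the source and a one-line edit to the form in REDCap, with no added burden for parents. The seven-item mean uses data already collected.

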#### 15.2.2.7 Parent Socio-Demographics

Thank you for agreeing to be in this study. Our goal is to find ways to better support families during a child's treatment with chemotherapy. While we hope you will complete each item, if a specific question makes you feel uncomfortable, please select "prefer not to answer" when available, rather than leave it blank.

First, we will ask a few questions about you.

1. Your age in years \_\_\_\_\_
  2. The sex assigned to you at birth (please select one)
    - a. Female
    - b. Male
    - c. Intersex
    - d. Prefer not to answer
  3. Your race (please select one):
    - a. American Indian or Alaska Native
    - b. Asian
    - c. Black or African American
    - d. Hispanic or Latino
    - e. Middle Eastern or North African
    - f. Native Islander or Pacific Islander
    - g. White
    - h. Prefer not to answer
  4. What language do you speak at home most of the time?
    - a. English
    - b. Spanish
    - c. Other (please specify): \_\_\_\_\_
-

- 
5. What language do you use for medical conversations about your child?
    - a. English
    - b. Spanish
    - c. Other (please specify): \_\_\_\_\_
  6. What is the highest level of schooling?
    - a. Less than high school
    - b. High school
    - c. More than high school
  7. Please select the option that best describes your current marital status:
    - a. Married
    - b. Living with a partner
    - c. Single (living alone)
    - d. Separated or divorced
    - e. Widowed
  8. What is your current employment status?
    - a. Full-time (at least 30 hours per week)
    - b. Part-time (less than 30 hours per week)
    - c. Casual (as needed for short time periods)
    - d. Not currently working for pay
  9. To what extent have you or your child's other parent changed your employment situation because of child's diagnosis?
    - a. one of us works more hours than before
    - b. we both work same number of hours as before
    - c. one of us is working fewer hours than before
    - d. both of us are working fewer hours than before
    - e. one of us quit work or took family leave
  10. What type of insurance do you use to pay for your child's healthcare? (Select all that apply)
    - a. Medicaid or state-funded low-income insurance program (e.g., CHIP)
    - b. Private insurance (through work or school)
    - c. Private insurance (purchased directly)
    - d. Uninsured (self-pay)
    - e. Other (please specify, such as Tri Care): \_\_\_\_\_
  11. How often do you need someone to help you read instructions or other written material from your or your child's health care team or social workers?
    - a. Never
    - b. Rarely
    - c. Sometimes
    - d. Often
-

- e. Always
12. What is your relationship to the adolescent participating in this study with you?
- Parent
  - Other legal guardian

The next questions are about your household.

13. Please provide your best estimate of your household's gross annual income (income before taxes are taken out). Include income from wages, child support, rental properties and social security, disability, veteran's benefits, unemployment benefits, worker's compensation and other money paid to you.
- \$ \_\_\_\_\_
  - I don't have a regular income
  - Prefer not to answer

14. How many people does that income support?  
\_\_\_\_\_ Number of people  
\_\_\_\_\_ Not including the child receiving chemotherapy, how many of these people have health conditions that require extensive medical care, or help from you?

